
### Sample size

The power calculation is based on data from a pilot study (*N* = 8) as we have not identified any studies investigating the effects of ball blankets on TST in depressed patients.

The main outcome will be changes in total night-time sleep with and without PBB estimated by the means of the differences between the periods for each participant. The null hypothesis is that there is no change in sleep duration. In the pilot study, the mean sleep duration appeared normally distributed and the mean sleep duration without a ball blanket was 420 min. The standard deviation of the difference between the sleep duration with and without a ball blanket was 42 min. Based on the potential clinical gains, we aim to be able to detect a change in total sleep duration of 20 min. Assuming that the differences in sleep duration with and without a ball blanket is normally distributed, we performed power calculations for a paired *t* test, and with an alfa = 0.05 and power = 0.80 the minimum required sample size is *N* = 37. To take into account dropout rates, we aim to include 45 patients.

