### Statistical methods

Paired, two-sided analyses will be performed. If the differences in the measures between the exposure and control periods for each patient are normally distributed, as we expect, we will use a Student’s *t* test to test the null hypotheses of no differences. For the non-normal distributions, non-parametric tests, e.g. Wilcoxon signed-rank tests or Fisher’s exact tests will be used.

All data with or without protocol violation will be included in the analysis with complete outcome data for all randomized participants. Because the analyses are based on the differences between period A and B or B and A for each patient, we will perform complete case analysis (i.e. participants with missing actigraphic data from one of the periods will be removed from the analysis). An intention to treat analysis will be performed, i.e. patients that in one or both of the periods use an “incorrect”, non-study blanket will be kept in the analyses in their randomized sequence group. We will not account for missing data by imputation.

The level of statistical significance will be set to 5%.

The randomization will determine whether the participants will begin or end with a PBB. The baseline characteristics of these two groups will be presented in a table. Baseline information on sleep will be based on The Pittsburgh Sleep Quality Index (PSQI) and the Insomnia Severity Index (ISI) and not collected via actigraphy.

There will be no wash-out period in this trial because the PBB are expected to have no residual effect persisting in the subsequent periods. This assumption is based on the biological mechanisms of the ball blanket and on clinical experience, but there are no studies to corroborate this expectation. This aspect of the design, however, is expected to lead to bias toward the null, i.e. that the study will not overestimate a potential effect of PBB. The assumption of no carry-over effect in the data will be ruled out in a preliminary test. The sum of the TST values will be calculated for the time period when using PBB and when using patients’ own duvets for each participant. This will be compared across the sequence groups by means of an independent *t* test. If this test yields a statistically significant result, the usual test for differences between the effects of treatment A or B will not be applied [31].

Data will be analysed using Stata IC15 (Stata Corp, College Station, TX, USA).

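### The primary test of total sleep time is run only if a low-power carry-over pre-test is non-significant; that pre-test cannot rule carry-over out, and with no carry-over it still cancels the primary test in 5% of trials

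*Protocol article*

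**What the plan says.** The Statistical methods section of the protocol article announces a check for carry-over before the treatment comparison: "The assumption of no carry-over effect in the data will be ruled out in a preliminary test". Each patient's TST is summed over the blanket and duvet periods, and the sums are compared between the two sequence groups with an independent t test. If that test is significant, "the usual test for differences between the effects of treatment A or B will not be applied". The only significance level in the section is 5%.

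The same section says there is no washout, concedes that no study supports the absence of carry-over, and argues that any carry-over would pull the result toward the null.

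The Sample size section does not mention the pre-test. It states "we performed power calculations for a paired *t* test", aims at a 20 min change with an SD of differences of 42 min, and concludes that "the minimum required sample size is *N* = 37" for 80% power. Recruitment is set at 45 to allow for dropout.

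**The concern.** The rule makes the trial's only primary comparison depend on a different, weaker test. Three things are at stake.

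- **Reassurance.** The sum of two periods carries the between-patient variation that the crossover was chosen to remove. A non-significant pre-test would be read as showing no carry-over when it could hardly have shown anything else.
- **Chance cancellation.** A 5% test is significant in 1 trial in 20 when nothing is there. A chance difference in habitual sleep between two groups of about 20 patients is enough. Baseline sleep is not measured by actigraphy, so no objective baseline TST exists to recognise such an imbalance.
- **Consistency.** The sample size assumes a paired test that is always run. The Statistical methods section also argues that carry-over could only make that test conservative, yet it withholds the test when carry-over is suspected.

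**Working it through.** **Inputs from the protocol article.** Target difference 20 min; SD of the within-patient difference 42 min (pilot, N = 8); two-sided alpha 0.05; power 0.80; minimum N 37; planned recruitment 45; pre-test level 5% (the only level given).

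**Assumptions.** 1:1 allocation, so 18 and 19 patients per sequence at N = 37, and 22 and 23 at N = 45. Normal data with equal period variances. The between-patient SD of TST is not given, so a range is used.

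**1. The stated sample size.** For a paired two-sided t test the noncentrality is (20/42) × √n with n − 1 degrees of freedom. At n = 37 it is 0.476 × 6.083 = 2.90 and power is 80.5%. At n = 36 power is 79.3%. The stated N = 37 is reproduced for a test that is always run.

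**2. The procedure as written, with no carry-over.** Under the assumptions, a patient's sum and difference are independent. The chance that the paired test is run and is significant is therefore 0.95 × its power.

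| Completers | Paired test always run | Paired test only after a non-significant pre-test |
|---|---|---|
| 37 | 80.5% | 0.95 × 0.8047 = 76.4% |
| 40 | 83.6% | 79.4% |
| 41 | 84.5% | 80.3% |
| 45 | 87.8% | 83.4% |

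Simulation (40,000 runs per scenario) gave 76.3% to 76.5% at N = 37. The rule needs 41 completers to keep 80%, that is at most 4 of 45 lost (8.9%). The plan allows for 8 of 45 (17.8%).

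**3. Power of the pre-test to find carry-over.** The within-period error SD is 42/√2 = 29.7 min. With between-patient SD s, the SD of the sum is √(4s² + 2 × 29.7²). A carry-over of λ min in period 2 of the AB sequence shifts the difference in mean sums by λ. The standard error is SD(sum) × √(1/18 + 1/19) = SD(sum) × 0.329, with 35 degrees of freedom. For λ = 20 min:

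| Assumed between-patient SD | SD of sum | Pre-test power at N = 37 |
|---|---|---|
| 30 min | 73 min | 12.7% |
| 45 min | 99 min | 9.2% |
| 60 min | 127 min | 7.5% |
| 75 min | 156 min | 6.7% |

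The case most favourable to the pre-test is zero within-patient correlation (s = 0), where the SD of the sum is also 42 min. Power is then 29% at N = 37 and 35% at N = 45.

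**4. What passing the pre-test leaves behind.** With a true effect of 20 min and a carry-over of 20 min, the paired estimate averages 20 − 20 × 19/37 = 9.7 min. In simulation at N = 37, 87% of such trials passed the pre-test at a within-patient correlation of 0.5 and 93% at 0.8. The mean estimate among those that passed was still 9.7 min.

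**5. Type I error.** With no effect and no carry-over, the paired test was significant in 5.0% of simulated trials that passed. The rule does not inflate the false-positive rate in that situation.

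**The case against.** The strongest reply is that the rule is cautious and costs little. The power figure is correct for the test it names, the loss is about 4 points, and 80% survives if 41 or more of the 45 patients complete. The protocol also does not rest on the pre-test alone: it gives a mechanistic reason for omitting washout and admits the lack of evidence. All of this stands, and it limits the size of the point. It does not make a non-significant pre-test informative, and 37 completers is the number for which the protocol claims 80%.

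The pre-test power also depends on an assumed between-patient SD. With zero correlation, the pre-test would have about 80% power at N = 37 for a 40 min carry-over. That is twice the target effect; for 20 min, power is low across the whole range.

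A reader might infer more than the document supports:

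- *That the rule inflates type I error through a first-period analysis.* The article contains no such fallback, and step 5 shows no inflation without one.
- *That a significant pre-test is as likely to be chance as carry-over.* That depends on how plausible carry-over is beforehand, which the article does not quantify.
- *That the trial would be left with no primary analysis at all.* The article says only that the usual test is not applied. What follows may be set out in the full protocol or the analysis plan, which are not shown.

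**Conclusion.** The point holds as a fault in a rule that the protocol states. The pre-test cannot rule out a carry-over as large as the target effect: its power is about 7% to 13% at 37 completers for between-patient SDs of 75 to 30 min, and no more than 29% (N = 37) or 35% (N = 45) at any non-negative within-patient correlation. With no carry-over, the rule withholds the primary test in 5% of trials and lowers the chance of detecting 20 min to between 76.4% (37 completers) and 83.4% (45).

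The rule also contradicts the protocol's own bias argument. If carry-over can only shrink the difference, a significant A-versus-B result remains credible when carry-over is present, and there is no reason to withhold the test.

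The 5% and the power figures for the procedure as written rest on the protocol's inputs, normality, equal period variances and no carry-over. The pre-test power figures also rest on 1:1 allocation and on the assumed between-patient SD or correlation.

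**What to change.** Delete the condition. State that the prespecified within-patient A-versus-B contrast of TST is run and reported as the primary result in every case.

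Replace the claim that a preliminary test rules out carry-over with two items:

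- the between-sequence contrast of summed TST, reported descriptively with a confidence interval and with no consequence for the primary test;
- a sensitivity analysis that excludes the early nights of period 2, and the matching nights of period 1 for symmetry, from the actigraphy already recorded. The number of nights should be fixed before the data are seen. This analysis is informative only if carry-over fades within those nights.

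If the condition is kept, restate the power for the two-step procedure: 76.4% at 37 completers, with 41 needed for 80%.

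The cost is a wording change and one extra analysis run, with no new data. The sensitivity analysis will be slightly less precise because it uses fewer nights.

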### Data monitoring

No data monitoring committee (DMC) will be established for this trial. Further, no interim analysis will be performed due to the short duration of the trial and a minimal intervention risk.

## Discussion

This trial has some limitations. First, we use the PSQI four times during the trial. For the purpose of screening for eligibility and again at visits 2, 3, and 4. However, PSQI is a retrospective 30-day instrument and there will be less than 30 days between assessments at visits 3 and 4 (14 days to be precise) [3]. However, there will be no overlap in the recall periods between visits, as patients are asked about their sleep quality during the past 14 days at these particular two visits using a modified version of the PSQI. This is not expected to cause any bias to the results and interpretations of these as a duration of 2 to 3 weeks is often recommended clinically to differentiate transient from persistent sleep-wake disorders [3]. Most importantly, the PSQI with a 1-month recall period will be used as suggested when screening for eligibility and again at visit 2, which will enable us to separate the transient sleep-wake problems from the persistent sleep-wake problems when recruiting patients for this trial [3].

Second, remission in the underlying depression condition may occur during the trial. In order to minimize the chance of remission and to ensure a constant intensity during both periods (AB and BA), we have chosen a short intervention period. The condition is less likely to develop radically compared to when there are long treatment periods.

Third, patients in outpatient clinics are often in need of acute treatment. Therefore, period effects may occur due to newly introduced medication or medication adjustments during the trial period. Nevertheless, patients will not be excluded from the study due to these conditions as recruitment will then become almost impossible. Besides, such conditions will be equally distributed between sequence groups A-B and B-A due to the randomization. In order to interpret the results critically, we register medication prescriptions at baseline and again in sleep diaries if any changes are made during the trial period.

In summary, this is a randomized crossover multicentre trial testing the efficacy of Protac Ball Blankets™ on insomnia in depression treated in an outpatient setting. An easy identification of the included patients by clearly defined inclusion criteria, together with the multicentre design, supports the broad clinical relevance of the study results. Because both treatments are evaluated for the same individual, the treatment effect can be estimated based on an average of within-individual differences. Hereby, the crossover design removes between-patient variation and patients can indicate clear preferences for PBB vs regular duvets. The outcome of this trial is of high interest as the PBB may be a potential non-pharmacological supplement to medical treatment of patients with insomnia due to depression.

## Trial status

Recruitment of participants began on November 21, 2019, and will be completed in May 2021. The manuscript reports protocol version 5, October 9, 2019.

The results will be submitted for publication in an international peer-reviewed open access journal in Spring 2022. Authors will have to meet the principles of the Vancouver Declaration. The results will be presented at both national and international conferences, fairs, and hospitals. Furthermore, the results will be presented at national and international business collaboration meetings by means of Protac A/S contacts. An e-mail will inform the patients about test results if requested.

## Data Availability

Not applicable.

## Abbreviations

AMI: Ambulatory Monitoring Inc.
BAI: Beck Anxiety Index
HAM-D6: 6-Item Hamilton Rating Scale for Depression
ISI: Insomnia Severity Index
MDI: Major Depression Inventory
PBB: Protac Ball Blanket™
PIM: Proportional Integrating Measure
PSQI: The Pittsburgh Sleep Quality Index
SCL-28: Self-reported Symptom State Scales
SOL: Sleep onset latency
TST: Total sleep time
WASO: Wake after sleep onset
ZC: Zero Crossing
